##### Inflammatory markers

Enzyme-linked immunosorbent assays (ELISAs) will be used to measure concentrations of IL-1β, IL-2, IL-6, IL-8, TNFα, IFN-γ, IL-10, IL-12p70, IL-13, and IL-4 (multiplex Proinflammatory Panel 1, Meso Scale Discovery, Rockville, MD) [66], IL-1α (Meso Scale Discovery, Rockville, MD) [4, 9, 14], prostaglandin E2 (PGE2; R&D Systems, Minneapolis, MN) [67], and monocyte chemoattractant protein-1 (MCP-1; R&D Systems, Minneapolis, MN) [68] in both the serum and synovial fluid.

##### Cartilage remodeling

Following ACL injury, proteoglycan loss progresses as evidenced by a decrease in synovial fluid GAG [69]. This loss in proteoglycan content has been reported to be followed by a subsequent onset of collagen damage and an increase in the synovial fluid concentration of biomarkers of type II collagen breakdown (CTXII) with CTXII released into the synovial fluid and the circulation [69]. Urinary CTXII has been identified as a biomarker for the diagnosis, staging, and evaluation of the prognosis of hip and knee OA [70, 71] and has also been demonstrated to be responsive over short testing periods (3 months) [72]. We have reported that CTXII correlates with the degree of joint destruction and increases significantly within 1 month after ACL injury [4, 9]. In addition to markers of cartilage degradation, we will also assess a biomarker of type II collagen synthesis in the serum and synovial fluid (N-terminal propeptide of collagen IIA (PIIANP) as low-serum PIIANP has been predictive of clinically relevant progression of both OA symptoms and cartilage degradation [64].

Synovial fluid concentrations of GAG will be quantified using a commercial kit per the manufacturer’s instructions (Kamiya Biomedical Company, Seattle, WA, USA) as previously described [69]. CTXII will be measured in the urine by ELISA (Cartilaps® (CTX-II); Immunodiagnostic Systems, Inc, Fountain Hills, AZ) [4, 9] and will be normalized to creatinine levels (Quidel, San Diego, CA) [64, 73]. PIIANP will be measured in the serum and synovial fluid by ELISA (Merck Group/Millipore, EZPIIANP-53 K, [64]).

##### Bony remodeling

CTXIα is localized to areas of high turnover of subchondral bone [73] and has been found to be predictive of OA symptom and radiographic progression [64]. CTXIα will be measured in the urine by sandwich ELISA (Nordic Biosciences, Herlev, Denmark), and like CTXII, will be normalized to urinary creatinine levels [64, 73].

#### Rigor and reproducibility

Biomarker data collected will be analyzed with respect to variability, linear range of standard, and need for repeat analyses. Controls provided with commercially available ELISA kits will be used with every run. For assays for which no control is available or provided, aliquots of serum from normal human subjects have been aliquoted and frozen at – 80 °C for this purpose. Each assay day, a fresh aliquot of this control serum is thawed and used on every plate to calculate intra- and inter-assay variance of the assay. In addition to the standard curve run in duplicate for each assay, this control will be run with each assay and the results used to determine the precision of the assay and to establish an acceptable control range for the assay. The mean of the control sample for all assays plus or minus two standard deviations is defined as the acceptable control range. Any samples on a plate in which the control falls outside of this range will be excluded and repeated. Samples will be run in duplicate and reanalyzed if the coefficient of variation is greater than 15%. For values that are below the level of detection as defined by the lowest standard, a value equivalent to 0.5 lowest limit of detection will be recorded and used for statistical analyses. To ensure data quality and fidelity, all data collection and analysis procedures will be detailed in a structured manual. The full research team will attend half-day training sessions both prior to study initiation and following enrollment of the first three patients have been enrolled to identify unforeseen issues that may arise and will also convene quarterly throughout the study period.

For cartilage T_1ρ_ and T_2_ quantification, we have published excellent scan/re-scan reproducibility in human subjects with coefficients of variation (CV) < 4% for single vendor settings [74] and CV < 10% for multi-vendor settings [75] using the MAPSS sequences [76]. Longitudinal CVs of monthly collected phantom T_1ρ_ and T_2_ have been reported < 3% [74]. In this study, a T_1ρ_ and T_2_ phantom will be scanned monthly at each site for the duration of the proposed study. SNR, intra-day reproducibility, and inter-day reproducibility will be quantified. Longitudinal data will be examined for any potential shift of quantified parameters. If more than 3% of relaxation time shift is observed, acquisition of subjects will be put on hold until discrepancies can be resolved.

### Statistical analysis

#### Primary aim analysis

Inflammatory biomarkers PGE2 and MCP-1 concentrations will be assessed for normality [12, 66]. If not normally distributed, biomarker concentrations will be transformed using Box-Cox transformation [66]. A 2 × 4 repeated measures ANOVA (group × time) will be used to assess changes in biomarker concentrations between the montelukast and placebo groups.

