**Methods:**

We will enroll 30 individuals undergoing primary ACL reconstruction to participate in this IRB-approved multicenter clinical trial. This trial will target those at greatest risk of a more rapid PTOA onset (age range 25–50 with concomitant meniscus injury). Patients will be randomly assigned to a group instructed to take 10 mg of montelukast daily for 6 months following ACL reconstruction or placebo. Patients will be assessed prior to surgery and 1, 6, and 12 months following surgery. To determine if montelukast alters systemic inflammation following surgery, we will compare systemic concentrations of prostaglandin E2, monocyte chemoattractant protein-1, and pro-inflammatory cytokines between groups. We will also compare degradative changes on magnetic resonance imaging (MRI) collected 1 and 12 months following surgery between groups with reductions in early biomarkers of cartilage degradation assessed with urinary biomarkers of type II collagen breakdown and bony remodeling.

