### Design and setting

This is a multicenter, superiority RCT with parallel group assignment and 1:1 allocation ratio to assess the use of montelukast after ACL reconstruction. The study has been approved by both the University of Kentucky and University of California San Francisco institutional review boards. Details of the study design are set out in Fig. 1 according to the Standard Protocol Items: Recommendations for Interventional Trials (SPIRIT) Statement [41]. The SPIRIT Checklist can be found in Additional file 1. Participants will be enrolled at two academic medical centers (University of Kentucky and University of California San Francisco) with study-related analyses being performed at the Cleveland Clinic and Duke University. Important protocol modifications will be communicated to the investigative team through regular weekly meetings. It will be the PI’s responsibility to update participants or trial registries on any protocol modifications.

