#### Biomarker analyses

Blood and urine specimens will be collected on the day of surgery and all postoperative study visits to determine concentrations of the following biomarkers of inflammation, NFκB activation, cartilage degradation, and bone turnover. The selected urinary biomarkers have been shown to be predictive of inferior clinical outcomes and cartilage thinning [14, 64]. These validated biomarkers allow accurate assessment of cartilage degradation and bony remodeling and will be performed at the Duke Molecular Physiology Institute’s Biomarkers Shared Resource. In addition, both the involved and contralateral knees will be aspirated and synovial fluid collected on the day of surgery to assess inflammatory mediators and biomarkers of cartilage degradation. To avoid dry aspirations and missing data, the knee aspirations will be performed with a 5-mL saline lavage and normalized to urea content [65]. We anticipate that increased synovial fluid concentrations of a biomarker of proteoglycan loss (glycosaminoglycan (GAG)) and inflammatory mediators at the time of surgery would be predictive of increased MRI evidence of cartilage degradation postoperatively for the control group but would not be associated with increased cartilage changes in the montelukast group should that treatment be effective.

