#### Secondary aim analysis

Variables will be assessed for normality and if normally distributed, baseline and 1-year T1ρ and T2 relaxation times as well as bone shape changes will be compared between groups using a 2 × 2 repeated measures ANOVA (group × time). Based on previous work, it is expected that the biomarkers of type II cartilage breakdown (CTXII) and bony remodeling (CTXIα) will not be normally distributed and it is anticipated that biomarker concentrations will be transformed using Box-Cox transformation [66]. A 2 × 4 repeated measures ANOVA (group × time) will be used to assess changes in biomarker concentrations between the montelukast and placebo groups. The ordinal semiquantitative MOAKS data will be compared between groups using chi-square or Fisher exact tests as appropriate.

For both primary and secondary analyses, in the case of participants that violate group allocation, we will perform Intention-to-Treat and Per Protocol analyses. We will not employ imputation methods in the case of missing data. No interim or other subgroup analyses will be performed.

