#### Relevant covariates

Covariates known to influence the selected biomarkers will be collected and included as covariates in the statistical analyses which include patient age, biological sex, and race [77]. The location of significant differences will be determined using post hoc tests with a Bonferroni correction.

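### The 2 × 4 biomarker ANOVA treats the pre-randomisation sample as an outcome level; using it as a covariate in a mixed model on all available samples would gain power and keep participants with a missed sample

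*Protocol article*

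**What the plan says.** All references are to the protocol article.

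- **Test.** Primary aim analysis, for PGE2 and MCP-1: a repeated-measures ANOVA, two groups by four times, "will be used to assess changes in biomarker concentrations between the montelukast and placebo groups". Secondary aim analysis repeats the same test for CTXII and CTXIα.
- **Time levels.** The abstract gives four: "Patients will be assessed prior to surgery and 1, 6, and 12 months following surgery". Biomarker analyses places the first sample at surgery: "Blood and urine specimens will be collected on the day of surgery and all postoperative study visits". The Randomization section allocates only after the intraoperative findings and the 10-day wound check, so this first sample precedes allocation.
- **Missing data.** Secondary aim analysis, for both aims: "We will not employ imputation methods in the case of missing data".
- **Covariates and follow-up tests.** Relevant covariates lists those "included as covariates in the statistical analyses which include patient age, biological sex, and race". The baseline biomarker value is not among them. The section continues: "The location of significant differences will be determined using post hoc tests with a Bonferroni correction".
- **Replacement.** Study stopping rules and Randomization exclude and replace anyone who discontinues before the 6-month visit.

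**The concern.** The day-of-surgery value cannot carry a treatment effect. As an outcome level, its noise enters the group × time comparison in full. As a covariate, it would explain part of the variance of the later values. With 30 patients that precision matters, and the sample is already being collected.

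A conventional repeated-measures ANOVA also needs a complete row for each participant. With imputation ruled out, one missed draw would remove the participant's other samples too. The analysis would then rely on the complete cases being a random subset (missing completely at random), whereas a likelihood-based mixed model needs only missing at random.

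**Working it through.** **Inputs from the document.** 15 per arm; four visits, one of them before treatment. The Power analysis section gives an SD of 2.86 ms, a difference of 3.09 ms and 81.5% power for the change in T1ρ.

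**The plan's own figure.** 3.09/2.86 = 1.080. A two-sample t-test with 28 df and two-sided α 0.05 (not stated, assumed) gives 81.49%, so 81.5% reproduces. It is a power for T1ρ change. The 2 × 4 biomarker test has no power statement.

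**Assumptions.** The document gives no biomarker SD, correlation or time course. I take SD 1 at each visit, compound symmetry with r = 0.3, 0.5 or 0.7, and two-sided α 0.05. Age, sex and race are ignored on both sides.

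**Planned interaction test.** With d the arm differences in SD over four visits (d = 0 at baseline):

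λ = (15/2) × Σ(d − mean d)² / (1 − r), on F(3, 84), where 84 = 3 × 28.

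**Baseline-adjusted joint test** of the three post-operative differences:

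λ = (15/2)/(1 − r) × [Σd² − (r/(1 + 3r)) × (Σd)²], on F(3, 81), where 81 = 3 × 27.

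**Worked at r = 0.5**, where r/(1 + 3r) = 0.2:

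- Effects 0.5/1.0/0.5. Planned: Σ(d − 0.5)² = 0.5, λ = 7.5, power 60%. Adjusted: 1.5 − 0.2 × 4 = 0.7, λ = 10.5, power 76%. A month-1 peak (1.0/0.5/0.5) has the same sums and so the same two powers.
- Flat 0.8. Planned: Σ(d − 0.6)² = 0.48, λ = 7.2, power 58%. Adjusted: 1.92 − 0.2 × 5.76 = 0.768, λ = 11.52, power 80%.
- 0.8 at month 6 only. Planned: Σ(d − 0.2)² = 0.48, λ = 7.2, power 58%. Adjusted: 0.64 − 0.2 × 0.64 = 0.512, λ = 7.68, power 61%.

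| Effects, months 1/6/12 | Test | r = 0.3 | r = 0.5 | r = 0.7 |
|---|---|---|---|---|
| 0.5/1.0/0.5 | planned | 45% | 60% | 84% |
| 0.5/1.0/0.5 | adjusted | 70% | 76% | 90% |
| 0.8/0.8/0.8 | planned | 43% | 58% | 82% |
| 0.8/0.8/0.8 | adjusted | 78% | 80% | 91% |

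**Sensitivity to compound symmetry.** With an unstructured covariance on both sides, λ is unchanged but the error df fall to 26 (planned) and 25 (adjusted). For 0.5/1.0/0.5 the powers are then 41/55/79% against 65/71/86%. The levels drop, but the gain remains.

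**Single month-6 contrast**, baseline-adjusted: λ = (15/2) × d² / (1 − r²), on F(1, 27). At r = 0.5:

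- d = 1.0: λ = 10, power 86%, against 60% for the planned test.
- d = 0.5 (peak at month 1): λ = 2.5, power 33%, against 60%.

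**Missed samples.** If misses are independent at three post-operative visits, the complete fraction is (1 − m)³:

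- m = 2%: 0.941, so 30 × 0.059 ≈ 2 lost.
- m = 5%: 0.857, about 4 lost.
- m = 10%: 0.729, about 8 lost.

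**The case against.** **An omnibus test is a fair hedge.** The time course is unknown, and the section on postoperative administration stresses an inflammatory surge still present at 4 weeks. A reader might infer that a month-6 test would always beat the 3-df test. It would not: it loses 33% to 60% if the effect peaks at month 1. This part of the objection stands. It does not touch baseline adjustment, which helped the same 3-df question in each pattern above under compound symmetry.

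**Listwise deletion is not written.** This is true. It follows from a conventional fit without imputation, but the wording would also allow a likelihood-based fit. That is a reason to name the method.

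**The high loss figure is unlikely.** Minimizing attrition reports under 10% lost to follow-up in earlier trials, and participants who leave before month 6 are replaced. Losing 8 of 30 should not be read as the expected result. Intermittent missed samples and month-12 losses remain exposed.

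**Site.** Because "Participants will be enrolled at two academic medical centers", a reader might infer that omitting site from the model, or from the randomisation, is a flaw. The document does not support that. Biomarker assays go to one laboratory, and each type of quantitative image analysis is assigned to one group. An additive site shift cancels in within-patient change. The article is merely silent on stratification, which a condensed article may be.

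**The sizing outcome is not affected in the same way.** This stands. The 2 × 2 T1ρ interaction has 1 df and equals a t-test on change, so the 3-df and four-visit points do not apply. Its first scan is at 1 month, after dosing starts at about day 10. Using it as a covariate is equivalent only if it is accepted as a baseline.

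**Conclusion.** The point holds for the four biomarkers as a matter of efficiency. The planned interaction test is a valid randomised comparison, and no bias is shown beyond what selective missingness could cause. Under the assumptions stated, baseline adjustment adds roughly 6 to 35 percentage points of 3-df power when the effect is spread over the post-operative visits. It adds most at low correlation and little at high correlation. When the effect is confined to month 6 the gain is about 3 points at r = 0.5. All these sizes rest on assumed SDs, correlations and time courses. The complete-case loss depends on an unstated fitting method and an assumed miss rate, with 2 to 4 of 30 more plausible than 8. Because the change is inexpensive and the trial small, it should be made.

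**What to change.** For PGE2, MCP-1, CTXII and CTXIα, replace the 2 × 4 ANOVA with a likelihood-based linear mixed model on the (transformed) 1-, 6- and 12-month values. Include arm, visit, arm × visit, the pre-treatment value and its interaction with visit, and the planned covariates age, sex and race. State that all available samples are used without imputation, which keeps the sponsor's own rule. Test the arm differences at the three post-operative visits jointly, or by one contrast named before unblinding. A single month-6 contrast is better only if the effect is expected to be greatest then, so that choice is the sponsor's.

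The cost is a change of wording and standard software. The baseline slopes use three error df (84 to 81 in the working). The model recovers samples only from participants who stay in the analysis; it does not by itself change the rule that excludes and replaces those who leave before month 6.

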#### Secondary aim analysis

Variables will be assessed for normality and if normally distributed, baseline and 1-year T1ρ and T2 relaxation times as well as bone shape changes will be compared between groups using a 2 × 2 repeated measures ANOVA (group × time). Based on previous work, it is expected that the biomarkers of type II cartilage breakdown (CTXII) and bony remodeling (CTXIα) will not be normally distributed and it is anticipated that biomarker concentrations will be transformed using Box-Cox transformation [66]. A 2 × 4 repeated measures ANOVA (group × time) will be used to assess changes in biomarker concentrations between the montelukast and placebo groups. The ordinal semiquantitative MOAKS data will be compared between groups using chi-square or Fisher exact tests as appropriate.

For both primary and secondary analyses, in the case of participants that violate group allocation, we will perform Intention-to-Treat and Per Protocol analyses. We will not employ imputation methods in the case of missing data. No interim or other subgroup analyses will be performed.

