### Participants

Participants will include 30 individuals undergoing primary ACL reconstruction (15 in the treatment group and 15 in the placebo group). Potential study participants will be identified by members of the research team during regularly scheduled office visits at the University of Kentucky’s Orthopaedic & Sports Medicine or University of California San Francisco Sports Medicine Center. After being identified as a potential study participant, the patient will meet with a member of the research team coordinator. Provided that the patient meets all inclusion and exclusion criteria, a member of the research team will begin the process to obtain informed consent. As part of the consent process, patients will have the option to allow the investigative team to store their data and biological specimens for future ancillary studies. We routinely recruit subjects from these physicians’ practices using similar methods.

In March, 2020, the FDA required a Boxed Warning about serious mental health side effects for montelukast which includes the risks of suicidal behavior and other serious neuropsychological events [30]. Children and adolescents will be excluded from the current trial as neuropsychological side effects of montelukast have been reported to be more common in children and adolescents than adults [31, 32]. To further avoid the potential for exacerbation of a pre-existing psychological condition, we will also exclude those with depressive symptoms and those that endorse suicidal ideation at the time of enrollment. Psychological screening and safety monitoring will be described in more detail below.

This trial will specifically target those that may be at greatest risk of a more rapid PTOA onset (age range 25–50 with concomitant meniscus injury as evidenced on their clinical preoperative MRI and clinical exam) [33–35]. Those who are undergoing revision procedures will be excluded; however, patients will not be excluded if they have had a previous contralateral ACL injury and/or surgery. In doing so, we hope to address the needs of the most at-risk patients but also those in whom a treatment signal could be feasibly detected.

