### Data collection

#### MRI analyses

All subjects will undergo MRI examination at visit 4 (1 month after ACL reconstruction) and visit 6 (12 months postoperatively). At one of the enrollment sites, the average time between initial presentation to the orthopedic surgeon and the date of surgery is 9 days. As such, it is often difficult logistically for patients and/or their caregivers to attend a study-specific MRI visit preoperatively when they have already had to take time away from school or work to have the clinical MRI performed in order to confirm the original injury diagnosis. Thus, we will rely on the clinical MRI and clinical exam to determine eligibility and have opted to have the baseline research protocol MRI images collected 1 month postoperatively as this is more feasible for patients and this timing is consistent with other groups studying cartilage changes after ACL reconstruction [56].

At both enrollment sites, sagittal and axial MRI images will be acquired using a 3.0-T MRI scanner and an 1Tx/15Rx phased array knee coil/flex coil. Sagittal and axial T1-weighted fast spin echo images (FSE) will be acquired to allow semiquantitative analysis at the conclusion of the study. These sequences will be followed by a sagittal high-resolution 3D dual echo steady state (DESS) sequence for cartilage segmentation and a sagittal combined T1ρ/T2 mapping for the quantification of cartilage composition. The major parameters for the DESS sequences are as follows: FOV = 140 mm, matrix = 384 × 307 × 176, resolution = 0.36 × 0.45 × 0.7 mm^3^, time of repetition (TR)/time of echo (TE) = 17.6 ms/6.0 ms. The T1ρ/T2 mapping will be acquired using a 3D MAPSS sequence with major parameters: FOV = 140 mm, image matrix = 320 × 160 × 24, resolution = 0.44 × 0.44 × 4 mm^3^, time of recovery = 1.5 s, bandwidth = 400 Hz/Pixel, TR/TE = 7 ms/3 ms, time of spin lock (TSLs) = 0, 10, 40, 80 ms for T1ρ mapping and preparation TEs = 0, 20, 40, 60 ms for T2 mapping. The scan time will be approximately 12 min for the combined T1ρ/T2 mapping. Images will be obtained with the knee in full extension.

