Images collected at the University of Kentucky will then be transferred digitally to the University of California, San Francisco (UCSF) to be analyzed in the [name] Lab which is part of the Musculoskeletal and Quantitative Imaging Research Group (MQIR) at UCSF. Based on the high-resolution DESS images, articular cartilage will be segmented using a spline-based, semiautomatic technique. The T1ρ map will be created on a voxel-by-voxel basis using established fitting routines. The segmented masks will then be overlaid on the T1ρ maps after registration between DESS and T1ρ images, and mean T1ρ values will be calculated for the entire tibiofemoral cartilage, medial and lateral tibial plateau, medial and lateral femoral condyles, and the patellofemoral compartment will be calculated. Semiquantitative analyses will also be performed to assess abnormalities of the cartilage, meniscus, and bone marrow by an experienced musculoskeletal radiologist using the MRI Osteoarthritis Knee Score (MOAKS) [57].

In addition to assessing cartilage changes on MRI, we will also assess bone shape changes after ACL reconstruction. The bone area of the medial femoral condyle has been shown to increase within the first few months after ACL reconstruction [58, 59]. This is clinically meaningful as similar bony changes have been previously associated with progressive OA and within 6 months of ACL reconstruction correlated with subsequent patient-reported outcomes and MRI markers of cartilage quality at 3 years [58, 59]. [name] group at the Cleveland Clinic has previously established the methods to assess bone shape changes after ACL reconstruction [59]; images from both enrollment sites will be transferred digitally to the Cleveland Clinic for analysis.

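### MOAKS grades, which the protocol calls ordinal, are assigned to tests that ignore grade order; at 15 per arm this loses power for an ordered shift and gives no direction or effect size

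*Protocol article*

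**What the plan says.** The MRI analyses section describes the readings: "Semiquantitative analyses will also be performed to assess abnormalities of the cartilage, meniscus, and bone marrow", scored by one radiologist on MOAKS. The scan schedule there is "All subjects will undergo MRI examination at visit 4 (1 month after ACL reconstruction) and visit 6 (12 months postoperatively"), and the same section treats the 1-month scan as the research baseline.

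Secondary aim analysis gives the test: "The ordinal semiquantitative MOAKS data will be compared between groups using chi-square or Fisher exact tests as appropriate". The choice left open is between two unordered tests. No ordered method is named, nor is the quantity to be tabulated (12-month grade, change in grade, or worsened/not worsened). In the same paragraph T1ρ, T2 and bone shape are to be "compared between groups using a 2 × 2 repeated measures ANOVA (group × time"), which uses both scans.

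The Aims section states the hypothesis in one direction: less degradative MRI change at one year with montelukast. The abstract describes the comparison this way: "We will also compare degradative changes on magnetic resonance imaging (MRI) collected 1 and 12 months following surgery between groups". The planned size is "15 in the treatment group and 15 in the placebo group". The Power analysis section covers only T1ρ of the medial femoral condyle.

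**The concern.** A chi-square or Fisher exact test on a table with several grades asks whether the two distributions differ in any way. It cannot tell a shift toward better grades from a scatter of grades, and it returns a p-value without direction or effect size. The question posed is directional. With four grades the unordered test spreads its sensitivity over 3 degrees of freedom, where an ordered test concentrates on one.

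With 30 patients, a non-significant unordered result and no effect estimate would say little about structural change. Because the article names the test, an analysis plan that follows it would inherit the mismatch.

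A second, smaller gap is that the sentence leaves open how the 1-month MOAKS grade is used, although that scan is available and is used for the continuous measures.

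**Working it through.** **1. The plan's own figure.** No power is stated for MOAKS. The only stated power is 81.5% for T1ρ (difference 3.09 ms, SD 2.86 ms, 15 per arm). Effect size: 3.09 / 2.86 = 1.08. Noncentrality: 1.08 × √(15/2) = 2.96. A two-sample t-test with 28 df at two-sided 0.05 gives 81.5%, so the figure reproduces. Two-sided 0.05 is not stated but is assumed below because it yields this match.

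**2. Neither test uses order.** With equal arms and counts a_k and b_k in grade k, Pearson's statistic is Σ (a_k − b_k)² / (a_k + b_k). Reordering the grades leaves the sum unchanged. Fisher's exact test on an r × c table has the same property.

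**3. Power cost, latent shift.** From the documents: 15 per arm, and 1.08 borrowed from T1ρ as one plausible shift. Assumed: three or four grades, the placebo distributions shown, a smaller shift of 0.8, and complete data. A normal variable is shifted and cut into grades; 6,000 simulated trials per row. Relative loss = 1 − (power of unordered test / power of Wilcoxon), taken before rounding.

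| Placebo grades | Shift | Chi-square | Fisher | Wilcoxon | Loss, chi-square / Fisher |
|---|---|---|---|---|---|
| 4 even | 0.8 | 31.8% | 32.4% | 48.2% | 34% / 33% |
| 4 even | 1.08 | 51.7% | 53.1% | 72.0% | 28% / 26% |
| 0.40, 0.30, 0.20, 0.10 | 0.8 | 26.2% | 29.0% | 43.8% | 40% / 34% |
| same | 1.08 | 42.2% | 45.8% | 65.4% | 36% / 30% |
| 0.55, 0.25, 0.15, 0.05 | 0.8 | 21.2% | 23.6% | 37.0% | 43% / 36% |
| same | 1.08 | 34.2% | 37.5% | 56.0% | 39% / 33% |
| 3 even | 0.8 | 37.2% | 33.5% | 45.2% | 18% / 26% |
| 3 even | 1.08 | 57.9% | 53.9% | 67.8% | 15% / 21% |
| 0.50, 0.30, 0.20 | 0.8 | 29.9% | 26.5% | 39.1% | 23% / 32% |
| same | 1.08 | 47.4% | 43.2% | 59.7% | 21% / 28% |

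**4. Power cost, proportional-odds shift.** Odds ratios 3 to 10.
- Four grades: the largest loss is 1 − 15.6/27.7 = 44% (chi-square; placebo 0.55, 0.25, 0.15, 0.05; odds ratio 3). The smallest is 1 − 78.3/91.2 = 14% (chi-square; placebo 0.10, 0.20, 0.30, 0.40; odds ratio 10).
- Three grades: from 1 − 76.1/85.0 ≈ 11% (chi-square, even grades, odds ratio 10) to 1 − 19.5/29.0 = 33% (Fisher; 0.50, 0.30, 0.20; odds ratio 3).

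**5. Where the cost vanishes or reverses.**
- Binary feature (60% against 15%): chi-square 76%, Wilcoxon 73%, Fisher 59%. There is no order to lose.
- Non-monotone effect (even grades against 0.05, 0.45, 0.45, 0.05): chi-square 47%, Wilcoxon 6%.
- No effect: rejection was about 4% to 6% for all three tests, so validity is not at issue.

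**6. Use of the 1-month grade.** Four grades, latent shift 0.8, Wilcoxon on the change against Wilcoxon on the 12-month grade alone:
- correlation 0.5: 33% against 45%
- correlation 0.8: 54% against 43%
- correlation 0.9: 67% against 42%

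On a continuous scale with equal variances, a change score has variance 2(1 − ρ)σ². That is below σ² only when ρ exceeds 0.5, and coarse grading weakens the correlation further. Adjustment for baseline gives (1 − ρ²)σ², which never exceeds σ². The documents give no correlation, so adjustment is the safer way to use the first scan.

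**The case against.** Four objections carry weight.

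- **The 1-month grade.** A reader might infer that it is discarded. The text does not say so. A Fisher test on categories of change would use it, and the abstract's wording points to change. What stands is only that the sentence does not fix its use.
- **Pre-existing lesions.** A reader might also infer that lesions present at the first scan would pass for treatment effects. With "parallel group assignment and 1:1 allocation ratio" they are balanced in expectation. If only 12-month grades were compared, they would add noise and chance imbalance, not systematic bias.
- **A fixed loss of one third.** This might be read off the simulations, but the documents do not support it. They give no number of grades, grade distribution or MOAKS effect. Fisher is also often the applicable test and can lose less. With four even grades and an odds ratio of 5, the treated proportions are 0.625, 0.208, 0.104 and 0.0625. Expected counts per arm are then about 6.6, 3.4, 2.7 and 2.3, so 6 of 8 cells fall below 5. In that setting chi-square has 44%, Fisher 48% and Wilcoxon 63%, and Fisher's loss is 1 − 48/63 = 24%.
- **Condensed article.** Details of what is tabulated may sit in a document not shown. That excuses the silence on grouping. It does not excuse the choice of test, which the article states outright.

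**Conclusion.** The point holds as one of efficiency and interpretability. Data described as ordinal, with a directional hypothesis, are assigned to tests that ignore order and give neither direction nor effect size. For an ordered shift at 15 per arm, the relative power loss against a Wilcoxon test is roughly 15-45% with four grades and roughly 10-33% with three. Those ranges rest on assumed grade counts, distributions and effects, complete data and two-sided 0.05.

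There is no loss for features reduced to worsened/not worsened, and an unordered test would do better against a non-monotone effect, though that is not the stated hypothesis. Type I error is not threatened, so it would be wrong to call the planned tests invalid. The article leaves the role of the 1-month grade open; it does not rule it out. Severity is minor: MOAKS is one of several secondary measures and has no stated power.

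**What to change.** Replace the MOAKS sentence so that each feature kept on more than two levels is analysed with an ordered method. The preferred choice is a proportional-odds model of the 12-month grade on treatment group and 1-month grade, reporting the odds ratio with its 95% CI. Name a Wilcoxon rank-sum test as the fallback where cells are too sparse to fit the model. Keep Fisher's exact test for features that are binary by definition. State which features and grade groupings are used, and settle all of this before unblinding.

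The cost is wording only, since both scans are already scheduled for every participant. There are four small downsides:
- The model assumes proportional odds.
- With 30 patients some grades may be too sparse to fit.
- An ordered method has less power if the effect is not monotone.
- The 1-month scan comes after study treatment starts at day 10 (Study stopping rules), so adjusting for it may remove a little early effect.
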